## Data management and analysis

### Data management

Before the study begins, all researchers receive comprehensive training on the protocol so that subjects have a clear understanding of the testing requirements subjects can better cooperate and provide more realistic information during the testing process. During the follow-up period, oral medications can be needed, but medications that may significantly interfere with the study results are prohibited from being used as auxiliary treatment. All medications should stopped 24 h before each follow-up assessment. If discomfort during the period, a remote program control should be carried out in time to adjust the stimulation parameters. The follow-up method is mainly outpatient follow-up. When irresistible factors occur, telephone contact and WeChat video connection can be temporarily used instead. However, during subsequent outpatient visits, all information obtained from the last non-outpatient visit must be shared with the patient. Check with your family members to ensure the authenticity and accuracy of the information. All researchers will use unified, standardized, normative, and internationally accepted assessment scales and case report forms (CRF). Before surgery, perioperatively, and 1 month, 3 months, 6 months, 9 months, and 12 months after surgery, blinded professional evaluators strictly followed the standardized evaluation scale and evaluation process to conduct evaluations and record standardized videos. Professional clinicians not related to this study will re-evaluate the scores at each follow-up time point and compare the scores obtained with the first score. If the difference is not significant, the first evaluation results will used. If the difference is too big, a third evaluation will performed. Once the assessment results are accurate, the recorder uploads the data to the case report form. During the data collection process, two data supervisors will review the contents of CRF to ensure the authenticity and accuracy of the data. If there are data errors or incomplete information, the data manager sends it back to the appropriate center, where the researcher checks the original file, rechecks, and updates the data. At the end of the trial, the data administrator will lock the database and send the data separately to two data analysts for analysis. During the research process, to ensure the quality and accuracy of the data, only designated personnel not related to this study can view and modify the data, and each modification will be recorded, and personnel related to this trial will remain evasive throughout the process.

### Data analysis

All data analysis will based on IBM SPSS Statistics 25.0, describing the total score of each scale at each follow-up and the change from baseline at each visit after treatment. Measurement data using mean ± standard deviation to describe. Count data Use numerical values (%) to describe, and use group t-test or Wilcoxon to compare between groups according to the characteristics of the data. Intra-group comparisons were performed using rank sum-test, paired t-test or paired signed rank-test. For comparisons of pre-and post-treatment change values based on baseline general information, appropriate multivariate analysis models were used to correct for the effects of confounding factors or covariates based on the data situation. The single-item count data of each scale used the chi-square test or the exact probability test, and the grade data used the Wilcoxon rank sum test. A paired rank sum test and repeated measures analysis of variance were used to analyze the changes in score data within the group before and after treatment. The effectiveness measurement index is the improvement rate of each clinical scale at different follow-up times = (scale score at each postoperative time point − preoperative score) / preoperative score * 100%. A score improvement rate > 25% is considered effective. Safety observation indicators are all postoperative adverse reactions, including surgery-related adverse reactions, device-related adverse reactions, and stimulation-related adverse reactions. The type, number of cases, occurrence time, treatment measures, and prognosis of adverse events are recorded. The incidence of adverse events is defined as the number of patients in which it occurs divided by the number of all patients, and an adverse event rate of less than 5% is considered safe.

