### Methods

#### Sample size

This study is a randomized, double-blind, active sham stimulation control design, and statistical experts determined that the sample ratio between the DBS group and the control group was 1:1. A review of the literature revealed that subjects’ upper limb FMA scores improved by an average of 7 points. Since this study was based on the changes in the mean FMA before and after DBS treatment, based on literature data, the mean FMA before DBS treatment was 21.92 ± 6.30, and the mean FMA after DBS treatment was 35.42 ± 12.23. This study is designed as a difference test to determine whether the mean of the DBS group (u1) is different from the mean of the control group (u2) (41, 42). The assumptions are as follows: H0: u1 − u2 = 0, H1: u1 − u2 ≠ 0. The two-sided significance level was 5%, the statistical power was 90%, and the dropout rate was 20% (43). The total sample size required for this study was calculated by PASS V.15 sample size calculation software to be 48 patients, with 24 people in each group. According to the possibility of electrode implantation deviation and other special circumstances leading to a lose, we included 62 patients, 31 in each group.

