#### Outcome measurements

All outcome measures will be evaluated by professional research assistants 1 week before surgery, during the perioperative period, and at one-month, three-month, six-month, nine-month, and 12-month intervals postoperatively (Table 2). All measurement results will be securely uploaded to a third-party online data management system. The primary outcome measure is the improvement in patients’ motor function before and after deep brain stimulation, assessed primarily through changes in the Fugl-Meyer Assessment Upper Extremity Scale (FMA-UE). Secondary indicators include the evaluation of patients’ balance function, neuropsychiatric behavior, fall risk, activities of daily living (ADL), and quality of life before, after, and at various time points following treatment, along with the calculation of the stroke improvement rate.

**Table 2 tab2:** Participant timeline of data collection.

Study period	Screening	Perioperative period		Follow-up period				
	Enrollment	Allocation/surgery	Postsurgery	1 month	3 month	6 month	9 month	12 month
Number of days	15 ± 7	10 ± 7	3 ± 2	7 ± 3	7 ± 3	7 ± 3	7 ± 3	7 ± 3

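### The between-group FMA-UE analysis does not fix preoperative FMA-UE as a covariate and leaves the model and covariates to be chosen from the data

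*Protocol article*

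**What the plan says.** The Data analysis section gives the between-group method as "use group t-test or Wilcoxon to compare between groups according to the characteristics of the data". The sentence opens with count data, but a t-test or Wilcoxon test can sensibly refer only to the scale scores. The section describes both totals at each visit and changes from baseline.

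For change values, it adds that "appropriate multivariate analysis models were used to correct for the effects of confounding factors or covariates based on the data situation". The adjustment is tied to general baseline information. No covariate is named, and no analysis is designated as primary.

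The baseline score is available. Outcome measurements says "All outcome measures will be evaluated by professional research assistants 1 week before surgery", and Table 2 marks FMA, BBS, POMA, BI, SF-36 and HAMD at screening. The same section defines the primary outcome as motor improvement "assessed primarily through changes in the Fugl-Meyer Assessment Upper Extremity Scale (FMA-UE"), so it is a change score.

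Randomization is simple 1:1, with no stratification stated. The Sample size section sets up a two-group comparison of means, "H0: u1 − u2 = 0, H1: u1 − u2 ≠ 0".

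**The concern.** Two things are at stake.

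- **Freedom of choice.** The test, the adjusted model and its covariates are all left to the data. Several different p-values could each be presented as the primary result of a trial in 62 implanted patients. Labelling the groups A and B (Blind method) hides the direction of an effect, but it does not stop an analyst from choosing covariates that enlarge a difference.
- **Unused baseline.** With simple randomization, the arms can differ in preoperative FMA-UE by chance. A comparison of totals carries that difference in proportion to the slope of follow-up on baseline score. A comparison of changes carries it in proportion to the slope minus 1. Fixing the baseline score as a covariate removes the dependence in either case and never has a larger asymptotic variance than the other two.

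**Working it through.** **Inputs from the Sample size section.** "the mean FMA before DBS treatment was 21.92 ± 6.30, and the mean FMA after DBS treatment was 35.42 ± 12.23"; "subjects’ upper limb FMA scores improved by an average of 7 points"; "The two-sided significance level was 5%, the statistical power was 90%, and the dropout rate was 20" per cent; 24 per group, raised to 31. The pre-post correlation ρ is not given, so I assume 0.2 to 0.8.

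**The plan's own figure.** A two-sample t-test (noncentral t) at 90% power gives:

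- effect 7, SD 6.30: 19 per arm; 19/0.8 = 23.75, so 24 per arm and 48 in total;
- effect 35.42 − 21.92 = 13.5, SD 12.23: also 19, then 24 per arm.

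Both pairings reproduce the stated 48, so the trial was sized for an unadjusted comparison. With 31 per arm, unadjusted power is 99.0% for either pairing. Adjustment can add at most about 1 point there.

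**Chance imbalance.** The SD of the baseline difference is 6.30 × √(2/31) = 1.60 points. The 95% range is ±1.96 × 1.60 = ±3.1 points.

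The slope of follow-up on baseline is ρ × 12.23/6.30: 0.39 at ρ 0.2, 0.97 at ρ 0.5 and 1.55 at ρ 0.8. For a baseline difference of 3.1 points:

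- totals are shifted by 3.1 × slope, that is 1.2, 3.0 and 4.8 points;
- changes are shifted by 3.1 × (slope − 1), that is −1.9, −0.1 and +1.7 points.

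**Power for a 7-point effect.** Follow-up SD 12.23, 31 per arm, two-sided 5%, parallel two-arm comparison:

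- totals: SD 12.23, power 60.2% at any ρ;
- change: SD = √(6.30² + 12.23² − 2ρ × 6.30 × 12.23), 60 df;
- ANCOVA: SD = 12.23 × √(1 − ρ²), 59 df.

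| ρ | SD change | Power change | SD ANCOVA | Power ANCOVA | ANCOVA minus change (points) |
|---|---|---|---|---|---|
| 0.2 | 12.59 | 57.7% | 11.98 | 61.9% | 4.2 |
| 0.3 | 11.96 | 62.1% | 11.67 | 64.2% | 2.1 |
| 0.4 | 11.30 | 67.0% | 11.21 | 67.7% | 0.7 |
| 0.5 | 10.59 | 72.6% | 10.59 | 72.6% | 0.0 |
| 0.6 | 9.84 | 78.7% | 9.78 | 79.1% | 0.4 |
| 0.7 | 9.02 | 85.2% | 8.73 | 87.4% | 2.2 |
| 0.8 | 8.12 | 91.6% | 7.34 | 95.9% | 4.3 |

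The gain over change scores vanishes where the slope is 1, at ρ = 6.30/12.23 = 0.515. If the baseline and follow-up SDs were both 12.23, which the article does not state, change-score power would be 41.8%, 60.2% and 93.9% at ρ 0.2, 0.5 and 0.8.

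**The case against.** The strongest reply has five parts.

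1. **The outcome is already a change score.** A reader might set 60% for totals beside 73% for ANCOVA at ρ 0.5 and infer that the plan gives away 12 points of power. The documents do not support that. Totals are not the stated primary outcome, and against change scores with the quoted SDs the gain at ρ 0.5 is nil. The 60% also pairs the 7-point effect with SD 12.23, which is not a pairing that yields the stated 48. The low starting power is therefore a sample-size question. This part stands and limits the size of the point.
2. **Adjustment is mentioned.** It would be wrong to read the plan as having none, because the sentence on change values covers the primary outcome. What remains is that the text lets the data choose the model and covariates.
3. **An article condenses the full plan.** A covariate list may well be left to a statistical analysis plan. Here, however, the article states a rule, that the data decide. That is a poor choice on the page, not an omission.
4. **Randomization protects against bias.** This is correct. A reader might infer that the unadjusted estimate is biased, but it is not on average. The harm is to precision and to the estimate given the imbalance that occurs. Nor is baseline FMA-UE unrestricted: criterion 7 requires a motor score of 50 to 84, and the lower limb contributes at most 34, so FMA-UE is at least 50 − 34 = 16. That bound is loose and leaves room for imbalance.
5. **The trial is a crossover.** In a within-patient contrast the patient's own level cancels, so most of the baseline argument and the ANCOVA gain fall away. This also stands. The figures above apply to a parallel comparison such as the first period, and a model with only treatment and baseline would be wrong for both periods together.

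**Conclusion.** The point holds in a limited form. The article names unadjusted between-group tests, leaves adjustment to the data, and does not fix a baseline score that every patient has. The lack of pre-specification does not depend on any assumed correlation and is the firmer half of the point.

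The precision half is modest. For a 7-point effect with SD 12.23 and 31 per arm, ANCOVA gives 62% to 96% power over ρ 0.2 to 0.8. That compares with 60% for totals and 58% to 92% for change, a gain over change of 0 to about 4 points. Under either pairing that reproduces the planned sample size there is almost nothing to gain. These figures assume ρ, normal data and a parallel comparison. Chance imbalance of up to about ±3.1 points (95% range) affects the estimate obtained in this trial, not its expectation.

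The change is worth making because it is nearly free and ρ is unknown in advance. The design and sample size need not change on this account.

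**What to change.** In Data analysis:

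- Pre-state the primary FMA-UE analysis. For the first-period between-group comparison, use a linear model with treatment and preoperative FMA-UE as a fixed covariate.
- Where both periods are used, specify a mixed model with treatment, period, sequence, patient and preoperative FMA-UE.
- Report the adjusted mean difference with its 95% confidence interval.
- Use the same form for BBS, POMA, BI, SF-36 and HAMD, each with its own preoperative score.
- Delete the wording that lets the data determine the covariates.
- Keep the t-test or Wilcoxon test as a sensitivity analysis.

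The cost is a change of wording and one degree of freedom for the baseline covariate. No new data are needed, and the models can be run in the stated SPSS software.

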## Methods and analysis

### Study design

The trial is a multicenter, prospective, double-blind crossover randomized controlled trial (RCT). The overall process is in Figure 2. In this study, we will include 62 moderate to severe post-stroke hemiplegia patients who had stable disease after 1 year of conservative treatment in multiple neuro medical centers in the General Hospital of the People’s Liberation Army of China et al. All patients included in the study will undergo deep brain electrode implantation. They will be randomly postoperatively divided into a DBS group and a control group, with 31 patients in each group. 1 month after surgery, the DBS group will be given electrical stimulation treatment, while the control group will undergo routine observation. Following up in the 3rd and 6th months after surgery. After the follow-up, all patients will stop electrical stimulation treatment for 2 weeks. After the 2-week washout period, the control group will start electrical stimulation treatment, and the DBS group will continue observation. Outpatient follow-up in the 6th and 9th months after surgery. After the follow-up, all patients will undergo electrical stimulation treatment. Observe for a long time. The leading outcome measure of follow-up is the pre-and post-change score on the Fugl-Meyer Assessment Upper Extremity Scale (FMA-UE). In addition, we will follow up on changes in the secondary outcomes of balance function, neuropsychiatric behavior, Post-stroke Spasticity, fall risk, activities of daily living, and quality of life.

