## Discussion

The study is currently being conducted at multiple centers including the Chinese People’s Liberation Army General Hospital. At present, research on the application of DBS in post-stroke motor dysfunction is gradually carried out (66). Slotty et al. (67) used GPi-DBS combined with Vim/ventral nucleus (Vop)-DBS to treat a case of unilateralism secondary to putamen stroke. In studies on patients with dystonia, the results showed that the patient’s motor symptoms were significantly and sustainably improved; Elias et al. included nine studies with a total of 32 patients with post-stroke dyskinesia and found that at least 13 of the patients received DBS treatment (12). Post-motor symptoms improved significantly. Koerbel et al. (68) reported a 48-year-old patient after a thalamic hemorrhagic stroke. After DBS zona incerta (ZI) treatment, the patient’s proximal motor function was significantly improved, the abnormal involuntary movement scale score was significantly reduced. Franzini et al. (15) reported that the motor function of 3 patients with post-stroke motor function deficits improved after DBS treatment of the contralateral internal capsule posterior limb. Baker et al. (7) used cerebellar dentate nucleus-DBS to treat 12 patients with moderate to severe upper limb motor deficits after unilateral stroke. The patients’ upper limb Fugl-Meyuer motor function score increased by 7 points, and the upper limb motor function improved. There was no improvement during the treatment. Serious complications occur. For patients with post-stroke motor dysfunction, the range of stimulation parameters is wide and needs to be adjusted individually according to the stimulation target. Existing literature shows that the optimal stimulation parameters must be determined individually for each patient. The optimal stimulation parameters have not yet been established. The conclusion is still under intense discussion. Paro et al. (12) systematically analyzed 82 DBS electrodes implanted in 53 patients and found that the voltage [M (range)] of 55 leads was 3.4 (2.4~4.0) V, the frequency [M (range)] of 63 leads is 145 (130~185) Hz, and the pulse width [M (range)] is 90 (60~120) μs. However, there are also studies showing that wider pulses (>400 μs) appear to be more effective in enhancing movement and more convenient than shorter pulse widths, and preliminary results from local field potential (LFP) measurements and behavioral tests suggest that lower stimulation frequencies (8–20 Hz) are more appropriate, therefore, we first stimulated with 20 Hz, 400 μs, 2.0–4.5 V pulse width, increasing voltage, and then adjusted the frequency and pulse width according to individual intraoperative behavioral responses. Although a large number of relevant studies have been carried out to initially confirm the unique advantages, effectiveness, and safety of DBS in patients with post-stroke hemiplegia, they are still at the stage of basic animal experiments, case reports and case series reports and large-sample RCTs have not yet been carried out. Research to confirm its effectiveness and safety. Based on this, we designed this research protocol. To our knowledge, this trial protocol is the first to explore the effect of MLR-DBS on improving motor function in stroke survivors. It is also the first RCT in the field of application of DBS in post-stroke motor dysfunction. Research proposal. This multicenter, prospective, randomized, double-blind crossover controlled clinical research protocol is the first to develop and execute a study on the safety, feasibility, and safety of deep brain stimulation (DBS) in the midbrain motor region (MLR) to improve motor dysfunction after stroke plan. The evaluation results were evaluated by random shuffling, and the first evaluation was blindly evaluated with standardized videos for comparison before and after to reduce potential bias. The randomization process of this study was carried out after the surgery of all patients, thus avoiding to a large extent the interference on the study results caused by the surgeon’s inability to implement blinding. Our research team has performed thousands of deep brain electrode implantation surgeries to treat Parkinson’s disease, dystonia, Major syndrome, and other diseases, and has rich clinical and surgical experience. The main purpose of this trial protocol is to improve wheelchair, subacute, and chronic stroke motor dysfunction through MLR-DBS and to study the clinical feasibility and efficacy of MLR-DBS in humans. Study results will demonstrate the effectiveness, efficacy, and safety of MLR-DBS in improving motor function in stroke survivors. Our goal is to maximize the long-term restoration of lost motor function in patients with severe movement disorders. This research program will guide on the importance of integrating existing and different rehabilitation techniques and designing more effective rehabilitation programs. The results of this trial will help to understand the neural mechanisms of MLR-DBS in stroke patients who develop hemiparesis after stroke. Provide clinical evidence support for the large-scale clinical application of DBS technology.

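### The stated tests are parallel-group and before-after tests that do not fit the crossover: they name no on/off contrast and no primary visit, and by randomised group the month 9 contrast is reversed or null

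*Protocol article*

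**What the plan says.** **Design.** The article calls the trial a randomised crossover. Under Study design, the DBS group is stimulated from month 1, all stimulation stops for 2 weeks after the month 6 visit, and then: "After the 2-week washout period, the control group will start electrical stimulation treatment, and the DBS group will continue observation".

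**Outcome.** Outcome measurements defines the primary outcome as improvement in "motor function before and after deep brain stimulation, assessed primarily through changes in the Fugl-Meyer Assessment Upper Extremity Scale (FMA-UE").

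**Analysis.** Data analysis describes each scale and its change from baseline at every visit. Between groups the instruction is to "use group t-test or Wilcoxon to compare between groups according to the characteristics of the data". Within groups: "Intra-group comparisons were performed using rank sum-test, paired t-test or paired signed rank-test", together with repeated measures analysis of variance. A rise of more than 25% over the preoperative score counts as effective. Unspecified multivariable models may correct for covariates, depending on the data. Under Blind method, the two groups carry fixed labels A and B into the analysis.

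**Sample size.** The hypothesis compares the mean of the DBS group with the mean of the control group.

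**The concern.** After the switch, the DBS group is on sham and the control group is stimulated. A two-sample test on the fixed group labels then no longer compares stimulation with sham in the intended direction. The named tests include nothing that follows stimulation state rather than group, nothing for period, and no visit at which the main comparison is made.

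The before-after tests have a different problem. Both groups have surgery and weekly guided rehabilitation, so a gain from the preoperative score can appear with no stimulation effect at all.

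For one and the same true effect, the text therefore allows contrasts that are positive, null or reversed, and it does not say which one decides the trial.

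**Working it through.** **1. The plan's own sample size.** Inputs from Sample size: two-sided 5%, power 90%, dropout 20%, 1:1 allocation, "upper limb FMA scores improved by an average of 7 points", and "the mean FMA before DBS treatment was 21.92 ± 6.30, and the mean FMA after DBS treatment was 35.42 ± 12.23".

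- Parallel two-sample test, difference 7, SD 6.30. Normal approximation: n = 2 × (1.960 + 1.282)² × (6.30/7)² = 17.0, so 18 per group. Noncentral t: 18 gives power 0.899 and 19 gives 0.915, so 19. With dropout, 19/0.8 = 23.75, so 24 per group and **48 in total, as stated**.
- Difference 13.5 (35.42 - 21.92) with SD 12.23 also gives 19, then 24 per group.
- Difference 7 with the pooled SD, √[(6.30² + 12.23²)/2] = 9.73, gives 42, then 53 per group, and does not reproduce 48.
- A paired formula needs a correlation r that the article does not give. For assumed r from 0 to 0.7 at difference 7, total N runs from 54 down to 25.

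The stated hypothesis (group mean against group mean) and the per-group count are those of a parallel comparison, and that comparison reproduces 48 with no further assumption.

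**2. What the group test estimates at each stage.** D is the true effect, c the share retained after washout (assumed; the article gives no value), and p1 and p2 are period effects common to both groups.

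- DBS first: period 1 = D + p1; period 2 = cD + p2.
- Control first: period 1 = p1; period 2 = D + p2.
- Group contrast (DBS minus control), period 1: D.
- Group contrast, period 2: cD - D = -(1-c)D.
- Average of the two group contrasts: cD/2.
- Standard crossover estimate: ½[D + (1-c)D] = D(1 - c/2).

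With D = 7, the average gain quoted in the article:

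| c | Month 6 | Month 9 | Average by group | Crossover estimate |
|---|---|---|---|---|
| 0 | 7 | -7 | 0 | 7 |
| 0.25 | 7 | -5.25 | 0.875 | 6.125 |
| 0.5 | 7 | -3.5 | 1.75 | 5.25 |
| 0.75 | 7 | -1.75 | 2.625 | 4.375 |
| 1 | 7 | 0 | 3.5 | 3.5 |

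**3. Month 12.** Three places disagree on who is stimulated:

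- Table 2 marks only the control group at months 9 and 12, so the contrast would be reversed as at month 9.
- Study design puts everyone on stimulation after the month 9 visit, so the contrast would be near 0 apart from order effects.
- The Abstract has both groups resuming at the month 9 and month 12 visits, which can be read either way.

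Study design also lists month 6 among the visits after the switch, although it places the washout after the month 6 visit. These passages must be reconciled.

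**4. Before-after tests.** If g is the gain from surgery, rehabilitation and time, the expected change at month 6 is D + g in the DBS group and g in the control group. A within-group test, or the 25% rule applied within a group, responds to g even when D = 0. Only the difference between groups isolates D.

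**The case against.** **The reversed test is assembled from parts.** The article never says that a month 9 difference by randomised group will be read as the treatment effect, and a negative period 2 difference between sequences is what a working crossover should show. This is fair: the reversal is conditional on analysing by label. But the fixed A and B labels point that way, and no other contrast is named.

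**Period and sequence terms belong in an analysis plan that is not shown.** Their absence alone would be no finding. Here, though, the article names its tests, and they suit another design. The covariate models are left to depend on the data and do not redefine the treatment contrast.

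**Stronger readings that a reader might infer, and that the article does not support:**

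- That month 12 also has the wrong sign. The schedule passages conflict, so this is not established.
- That carryover is expected and ignored. A 2-week washout is planned, and no passage predicts carryover. It is an inference from the stated aim ("Our goal is to maximize the long-term restoration of lost motor function") and from rehabilitation during stimulation. What is true is that the analysis makes no allowance for it. The two harms also trade off: the reversal shrinks to 0 as c approaches 1.
- That a rank-sum test is prescribed for paired data. The same section also speaks of a paired rank sum test, so this is loose wording.
- That 48 can come only from a parallel design. A paired formula also reaches 48 at an assumed r of about 0.15 (SD of the difference 12.89; 38 patients; 38/0.8 = 47.5). The stated hypothesis and per-group count settle the matter, not the total.

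**A period 1 primary analysis has limits.** With 24 completers per group and a difference of 7, power by the noncentral t is about 97% at SD 6.30, 69% at SD 9.73 and 49% at SD 12.23. Randomization also gives the DBS group remote guidance and the control group face-to-face guidance, so freedom from carryover is not freedom from every bias.

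**Conclusion.** The point holds and should be corrected before the analysis. The stated tests are parallel-group and before-after tests applied to a crossover, with no on/off contrast and no primary visit.

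- By randomised group, the month 9 contrast lies between -7 and 0 for a true effect of +7. This assumes D = 7, analysis by label, and c between 0 and 1.
- The month 12 contrast cannot be interpreted until the schedule is reconciled.
- Within-group results and the 25% rule are not evidence of a stimulation effect.
- Carryover is plausible but not documented. If present, it would pull a standard crossover estimate from 7 towards 3.5, while the period 1 group comparison is unaffected by it at any c.

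**What to change.** 1. State as primary the between-group difference in FMA-UE at month 6, the last visit before the switch in Table 2, by ANCOVA on the preoperative FMA-UE, adjusting for centre if numbers allow. This matches the stated null hypothesis and the parallel-group sample size.
2. Report the two-period on/off comparison as supportive: a mixed model with stimulation state and period as fixed effects and patient as a random effect. Say openly that two sequences over two periods cannot separate carryover from sequence, so this model still estimates D(1 - c/2).
3. Keep within-group tests and the 25% rule descriptive.
4. Reconcile the Abstract, Study design and Table 2 on the visits of each period and on who is stimulated after month 9, and only then define any month 12 contrast.

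Cost: the changes are to wording, with no new data. Period 2 becomes supportive, but the stated sample size makes no visible use of it. The power of the month 6 comparison depends on the SD, as shown above, so the SD assumption should be stated alongside it.

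### Repeated measures ANOVA, if run over all seven FMA visits, keeps only patients with every visit; a mixed model would use the scores it discards

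*Protocol article*

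**What the plan says.** The Data analysis section places everything in one package ("All data analysis will based on IBM SPSS Statistics 25.0") and names several methods for scale scores:

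- Between groups: "use group t-test or Wilcoxon to compare between groups according to the characteristics of the data".
- Within a group: "Intra-group comparisons were performed using rank sum-test, paired t-test or paired signed rank-test".
- Within a group, for scores before and after treatment: a paired rank test and "repeated measures analysis of variance were used to analyze the changes in score data within the group before and after treatment".
- With covariates: "appropriate multivariate analysis models were used to correct for the effects of confounding factors or covariates based on the data situation".

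The Sample size section states that "the statistical power was 90%, and the dropout rate was 20" per cent. It arrives at 48 patients and raises this to 62, mainly to allow for misplaced electrodes. The FMA row of Table 2 has seven assessments: screening, after surgery, and then, as Data management puts it, "1 month, 3 months, 6 months, 9 months, and 12 months after surgery". The Outcome measurements and Main outcome sections define the primary outcome as FMA-UE improvement from before to after stimulation.

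The article does not say which visits enter the ANOVA, which SPSS procedure will be run, or what happens when a visit is missing.

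**The concern.** Classical repeated measures ANOVA (the GLM repeated measures procedure in SPSS) needs a complete row for each patient. One missing visit removes the patient and every score already recorded for that patient. A patient seen at months 1, 3 and 6 who leaves at the crossover would then add nothing to the estimated gain at months 3 and 6.

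Two things are at stake. The first is precision, in a trial whose abstract already lists small size as a limitation. The second is possible bias: the patients who complete every visit may have gained more, or less, than those who leave. The design makes outcome-related dropout plausible, because the DBS group moves to sham in the second phase and the Discussion concedes that active stimulation is likely to be noticed. It does not show that such dropout will occur.

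**Working it through.** **Inputs.** From the article: 62 patients (31 per group), 20% dropout, seven FMA assessments, two-sided 5%, 90% power, a gain of 7 points, and means of 21.92 (SD 6.30) before and 35.42 (SD 12.23) after. The timing of dropout, its relation to outcome and the correlation between visits are not given; they are assumed below and shown as ranges.

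**1. The plan's own figure.** A two-sample t-test with difference 7 and SD 6.30 needs 19 per group. Difference 13.5 (35.42 − 21.92) with SD 12.23 also gives 19. Then 19 / 0.8 = 23.75, rounded up to 24 per group, 48 in total. The stated figure is reproduced, although the article does not say which difference and SD were paired. On that calculation, 2 × 19 = 38 completers are needed.

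**2. Patients kept if all seven visits enter.** 62 × 0.8 = 49.6, or 24.8 per group; 12.4 patients leave the analysis. If the 14 extra patients (62 − 48) were all lost for electrode reasons, 48 × 0.8 = 38.4 would remain, still the 38 the plan needs.

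**3. Recorded scores discarded.** If each of the 12.4 dropouts has k recorded visits, 12.4 × k scores are discarded out of 49.6 × 7 + 12.4 × k collected.

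| k | discarded | collected | share |
|---|---|---|---|
| 1 | 12.4 | 359.6 | 3.4% |
| 3 | 37.2 | 384.4 | 9.7% |
| 5 | 62.0 | 409.2 | 15.2% |
| 6 | 74.4 | 421.6 | 17.6% |

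**4. Precision.** Take the month 6 gain in one group and suppose every dropout leaves after month 6 at random. All 31 patients have the score but the ANOVA uses 24.8. The variance ratio is 31 / 24.8 = 1.25 and the standard error ratio is √1.25 = 1.12. If every dropout leaves before month 6, there are no month 6 scores to lose, only earlier ones.

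**5. Bias.** Let C be the mean gain in completers and D the mean gain in dropouts. The true mean is 0.8C + 0.2D and the completer estimate is C, so the bias is 0.2 × (C − D). For C − D of 0, 2, 4 and 7 points it is 0, 0.4, 0.8 and 1.4 points.

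**6. Illustration by simulation.** Assumptions: true month 6 gain 7, SD 6.30 at baseline and 12.23 afterwards, correlation 0.7 between visits, 20% dropout after month 3, 400,000 records per scenario.

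| Dropout | True gain | Completers only | Using earlier visits |
|---|---|---|---|
| Completely at random | 6.99 | 6.99 | 6.99 |
| Mildly related to month 3 change | 6.99 | 7.38 | 6.99 |
| Strongly related to month 3 change | 6.99 | 7.70 | 7.00 |

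The last column is right by construction, since dropout was made to depend only on observed scores. If it depended on unobserved scores, that estimate would be biased too.

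**The case against.** - **The article does not restrict the analysis to completers.** A reader might infer that it does. Listwise deletion is a property of the named method in its classical form, and it bites across all visits only if all seven enter one model, which is not stated. The analysis set and missing-data rule may stand in an analysis plan that is not shown, so their absence is no finding. This stands. What remains is the choice of method, which the article does make.
- **The treatment comparison does not rest on the ANOVA.** The null hypothesis in the Sample size section is tested between groups by t-test or Wilcoxon. This stands.
- **Paired tests are also named.** They need only the two visits compared, so a patient who leaves after month 6 still counts in a month 6 paired test. This stands, but the same within-group change could then be reported on two different patient sets, and the article does not say which governs.
- **Bias is not established.** A reader might infer that the gain will be overstated. With completely random dropout it is not, and patients are meant to be blinded. Large figures need extreme assumptions: a completer mean of 8.86 against a true 7 requires dropouts to average (7 − 0.8 × 8.86) / 0.2 = −0.44 points.
- **Sample size is adequate on the plan's own terms.** The 20% is already in the 48.
- **Sphericity** can be handled by standard corrections, so it is not a decisive argument against the ANOVA.

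**Conclusion.** The point holds in a limited form. Run classically on all seven FMA visits, the repeated measures ANOVA would keep about 50 of 62 patients at the planned dropout and discard 3.4% to 17.6% of the recorded assessments, depending on when patients leave. For a visit that all dropouts had attended, the variance of the gain is up to 25% larger than with all the available scores. Bias in the within-group gain is possible but conditional: zero under completely random dropout, and 0.2 times the difference in gain between completers and dropouts otherwise. Its size and direction cannot be known from the article.

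The documents do not support the stronger readings that the between-group result is affected or that the trial falls short of completers (49.6 against 38). The latter takes the plan's own calculation as it stands. The case for change is that a better method is available at little cost in the software already chosen.

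**What to change.** For FMA-UE and the secondary scale totals, replace repeated measures ANOVA with a linear mixed model (SPSS MIXED, REML) using all available visits from all randomised patients:

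- Fit visit as a category, with terms for treatment (the stimulation condition at each visit), period and sequence. Visit should be nested within period, because a full set of visit effects otherwise absorbs the period effect. The model then also estimates the between-treatment difference, which a within-group ANOVA does not.
- Use an unstructured covariance, with a simpler structure prespecified in case it does not converge. Seven visits give 7 × 8 / 2 = 28 covariance parameters with only 31 patients per arm, so the fallback may be needed.
- Keep the complete-case ANOVA, with a sphericity correction, as a sensitivity analysis.

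Before the period term can be coded, the article's visit schedule must be reconciled: Table 2 places the control group's stimulation phase at months 9 and 12, while Study design gives that phase's follow-up as months 6 and 9.

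The cost is a change of wording and slightly more modelling work, with no extra patients or data. The model's validity rests on data being missing at random, which should be stated.
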